### Study design

The EPOK trial is a two-arm exploratory double-blinded RCT with a 12-week intervention period, and the outcomes will be measured at baseline, 3 months, and 12 months. Figure 1 outlines the RCT phases. Eighty participants will be identified and randomly categorised into two groups: (1) MREP with transdermal oestrogen gel and (2) MREP with placebo gel. Eligibility will be assessed during screening. The Okayama University Hospital and Ochiai Hospital will conduct this trial. We have organised the EPOK trial team, including the Maniwa City Community General Support Center, which will assist with recruitment via telephone, mail, local newspapers, and public health seminars. The non-profit organisation (NPO) of the agri-garden project will assist with MREP coaching. Figure 2 outlines the trial design schedule following the SPIRIT guidelines [38].

**Fig. 1 Fig1:**
[figure not shown]
EPOK trial profile. Flow diagram summarizing trial profile through study phases

**Fig. 2 Fig2:**
[figure not shown]
trial design schedule. Study design schedule in accordance with the Standard Protocol Items: Recommendations for Interventional Trials (SPIRIT) Figure

### Participants

Eighty women will be recruited from the community in Maniwa City, Okayama, Japan. The EPOK trial eligibility criteria include:1)Women aged between 65 and 90 years when obtaining their consent.2)Participants with KOA with knee pain lasting ≥ 3 months.3)Those able to ambulate independently.

The exclusion criteria include [40]:

Disease diagnosed within the previous 2 years, including myocardial infarction, severe aortic stenosis, acute pericarditis, acute myocarditis, aneurysm, severe angina, clinically significant valvular disease, uncontrolled dysrhythmia, thrombophlebitis, pulmonary embolism, claudication, cerebral palsy, home oxygen therapy, psychotic illness, or depression, or conditions causing difficulty in exercising.Diagnosed with endometrial, ovarian, peritoneal, cervical, or breast cancers within the previous 5 years.History of upper or lower-limb bone fractures within the previous 6 months or 2 years, respectively.Bedridden condition for > 1 week within the previous 2 months, or for > 2 weeks within the previous 6 months.Inadequate intake.Renal impairment.Severe liver function disorder.Resting systolic pressure > 200 mmHg or resting diastolic pressure > 100 mmHg.Cognitive impairment.

### Study procedures

#### Recruitment

The potential participants will be recruited by medical practitioners and local social life support coordinators. Flyers and posters will be mailed to approximately 1000 seniors in 100 local senior groups, which exist as databases in the community support centre. In addition, the trial team will approach the senior worker group via telephone and mail the flyers.

### Screening and consent

Interested volunteers will be invited to attend an information session held by the chief investigator (CI) in each local district or senior group community. They will undergo screening via interviews using the medical history and exclusion criteria checklist. They can be screened via telephone if they cannot attend the interviews. If no obvious exclusion criteria exist, the volunteers will undergo a medical assessment as potential participants. All potential participants will provide written informed consent after the aim, treatment plan, anticipated benefit, and potential hazards of this trial are explained to them by the CI or sub-investigator. Furthermore, they will have the opportunity to ask questions during this time.

### Medical assessment

The potential participants will undergo a medical assessment after providing written informed consent, which will include medical history, clinical examination (knee, breast, and endometrial assessments), and cognitive assessment, to meet the inclusion and exclusion criteria. Medical history assessment will detail the current medical condition of the participant, including medication usage, family, past medical, and social (occupation and activity participation) histories, substance use/abuse (alcohol and smoking), and allergies. Knee radiographs and interviews regarding knee pain will be used for KOA clinical examination. If participants have already been diagnosed with KOA [41], they can skip the knee radiography. Participants will be interviewed regarding the location, duration, and pain intensity on a 0–10 visual analogue scale (VAS). Knee radiographs with Kellgren and Lawrence classification [42] of at least grade 1 (doubtful narrowing of the joint space with possible osteophyte formation) will be considered as positive. Patients with spontaneous knee pain in the previous three months and positive knee radiographs will be eligible for our trial. Breast and uterine endometrial examinations will be performed to minimise the complications of ERT [43], including mammography and ultrasonography, to exclude breast and gynaecological cancers. If a suspicious lesion is identified on breast examination or if endometrial thickness is > 5 mm [44], the participant will be excluded from the trial and referred for further examination. Resting blood pressure will be measured during the screening; participants with systolic pressure > 200 mmHg or diastolic pressure > 100 mm Hg will be excluded from the trial. Cognitive function tests will be performed using the Revised Hasegawa Dementia Scale. Participants scoring ≤ 20 on a 30-point scale, indicating a suspicion of dementia [45], will be excluded from the trial.

### Randomisation, allocation, and blinding procedure

Each participant will be enrolled in this trial by investigators after the medical assessment and matching the inclusion and exclusion criteria. The investigator will provide each participant with an identification code according to the case enrolment order and fill out a registration sheet, which includes the date of obtaining consent, any other information necessary to match the participant with the corresponding identification code, and the factors used for stratified randomisation.

The participants will be randomly categorised into two groups by an allocator who will not have contact with them throughout the trial: (1) MREP with transdermal oestrogen gel and (2) MREP with placebo gel. The participants will be stratified according to age (older: 75–89 years, younger: 65–74 years), physical activity (the intermediate steps taken in a week measured by a pedometer, higher ≥ 5000 steps per day, lower < 5000 steps per day), and knee extension strength (higher ≥ 18 kgf, lower < 18 kgf). The randomisation schedule will be computer-generated using the randMS® mobile application [46] (sold by [name], created using Filemaker® and Filemaker Pro Advanced®, ©2019 kazenoan) with a mixture of two or more block sizes. The allocator will send an email with the trial group allocation result and participant identification codes to an unblinded pharmacist who will fill the placebo gel into the supplement bottles and label them according to the group allocation. In the unlikely event of an adverse symptom requiring further medical investigation, the gel allocation details can be accessed by the investigator, and the patient will be excluded from the trial.

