### Statistical analysis

The MREP participants will be assigned to either the oestrogen or placebo group. Data will be aggregated for the assigned analysis participants at baseline, 3 months, and 12 months after the intervention. The target population will be the full analysis set, defined as all the randomised participants who have started their trial treatments.

The statistical analysis will be based on the intention-to-treat and per-protocol principles. The participants’ demographic background and baseline characteristics will be described as appropriate, with data presented as mean and standard deviation for continuous variables that appear to be approximately normally distributed, as medians and interquartile ranges for other continuous variables, and as counts and percentages for categorical variables. Linear regression analysis will be performed for a statistical comparison of the primary and secondary outcomes between the oestrogen and placebo groups. The relationship between the intervention and endpoints will be calculated as a regression coefficient with a 95% confidence interval. The covariate distribution is expected to be consistent across the groups due to randomisation. Therefore, only the presence or absence of intervention will be used as an explanatory variable for the linear regression analysis. However, the variable distribution will be biased by chance due to allocation; thus, the variable is added to the explanatory variables and an adjustment is made. We will adopt a complete case analysis as the primary analysis if the proportions of missing data are < 5%. Multiple imputations will be conducted if imputation of > 5% is required for the amount of missing data for an outcome, and the method will be reported.

The statistician, who is blinded to the allocation, will perform the analysis at the Department of Obstetrics and Gynaecology, Graduate School of Medicine, Dentistry, and Pharmaceutical Sciences, Okayama University. The validity of the analysis will be verified by the Centre for Innovative Clinical Medicine and Department of Epidemiology of the Okayama University as a third-party institution.

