### Outcome assessment

Outcome assessment will include baseline measurements of participants' anthropometric data and outcomes. At baseline, a physiotherapist will measure the height, weight, and upper arm, thigh, calf, abdominal, and gluteal circumferences and calculate the body mass index (BMI). The resting blood pressure and heart rate will be measured simultaneously. Outcome examinations will be performed at baseline before allocation, and 3 and 12 months after intervention initiation (Fig. 1). Outcomes will be measured by physical therapists with at least 5 years of clinical experience.

The primary outcome will be the 3-month and 12-month changes from the baseline physical performance according to the CS-30 score. The CS-30 devised by Jones is highly reproducible and has been shown to correlate with the quadriceps muscle strength and the ability to balance, walk, and perform ADL [61]. Since KOA-related knee pain reduces the ability to perform vertical movements, CS-30 is also reliable for functional assessment of inactivity due to KOA [62]. CS-30 uses an armless folding chair with a seat height of 40 cm. The participants will be seated in the middle of the chair with their back straight, feet shoulder-width apart, and arms crossed at the chest, and will be encouraged to complete as many full stands as possible within 30 s [61]. They will be instructed to sit fully between each stand. The measurer will silently count the correct stand completions after letting the participant practice once or twice.

The secondary outcomes include:Change in the knee pain score assessed using the VAS and 12-item Short form survey (SF-12).

VAS will be used to assess knee joint pain before and after the intervention. The pain intensity will be indicated by a 10 cm black line (the left end for ‘no pain’ and right end for ‘the greatest pain imaginable’) on the questionnaire, and the participant will be asked to draw a line to indicate the level of her current pain. Health-related quality of life as pain in daily life will be assessed using the SF-12, which was validated as a shorter alternative to the SF-36 [63].2)Change in physical function according to the gait speed and timed up and go test (TUGT)

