### Adverse events

The drug safety tests in this trial include liver and renal function tests, serum cholesterol levels, mammography, and gynaecological examination. Collection and examination of these parameters and all blood samples will be conducted at the Ochiai Hospital, Okayama, Japan. Participants will have 24-h access to call and visit the emergency department of Ochiai Hospital if any adverse event is suspected. A standardised protocol for potential adverse events will be available at the Ochiai Hospital with the CI’s contact number and a manual for examination and testing. All the adverse events will be recorded and monitored until the end of the trial. All significant and severe adverse events will be recorded in the clinical notes and written in a case report form, which includes the adverse event details, such as the timing of onset and resolution, extent, treatment, outcome, and severity assessment. Significant and severe events will be reported by the Okayama University Clinical Research Board (CRB) using the application form on the internet site. If participants have significant or severe adverse events, the CRB or CI will determine whether the participants can continue with or withdraw from the trial and inform them accordingly. These participants will be referred and treated for each event depending on the symptoms and severity, even if they are withdrawn from the trial.

The participants may report minor adverse events [58, 69] including:Reproductive organ: irregular vaginal bleeding, increased vaginal discharge, vulval irritation or itching, increased leiomyoma size, endometriosis recurrenceBreast: tender breastsSkin at site of gel application: redness, irritation, itching, pigmentation, hivesNervous system: headache, migraine, weakness, dizziness, depression, nervousness, rapid changes in mood, difficulty sleepingCardiovascular: palpitation, rise in blood pressureGastrointestinal: abdominal distension, nausea, abdominal cramps, vomiting, heartburnLiver function: increased liver enzymes (AST, ALT, alkaline phosphatase)Blood: decreased WBCs, anaemiaMusculoskeletal: back pain, lower limb, ankle, or finger swelling, arthritisOthers: Increased triglycerides, fatigue, tinnitus, nasal bleeding, weight gain

Significant adverse events [59, 70] include heavy vaginal bleeding, jaundice, heavy abdominal distension, and oliguria.

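### The code may be opened for any adverse symptom that needs a work-up, whether or not care depends on knowing the gel, so avoidable unblinding is possible and plausibly more frequent on oestrogen

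*Protocol article*

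**What the plan says.** The protocol article fixes the unblinding rule in one sentence of *Randomisation, allocation, and blinding procedure*. The trigger and the recipient are: "In the unlikely event of an adverse symptom requiring further medical investigation, the gel allocation details can be accessed by the investigator". The consequence follows at once: "and the patient will be excluded from the trial". The sentence calls the situation unlikely. It sets no severity threshold and no condition that treatment must depend on knowing the allocation.

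*Adverse events* sorts events into three grades:

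- **Minor events that participants may report:** these include irregular vaginal bleeding, tender breasts, raised liver enzymes and limb swelling, but also headache, dizziness, back pain, fatigue and skin irritation at the application site.
- **Significant events:** these "include heavy vaginal bleeding, jaundice, heavy abdominal distension, and oliguria".
- **Severe events:** signs of anaphylaxis or thrombosis.

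For significant or severe events, "the CRB or CI will determine whether the participants can continue with or withdraw from the trial and inform them accordingly". That section does not mention the code.

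On roles, *Transdermal oestrogen gel* has the chief investigator prescribe the gel. It also provides an unblinded pharmacist who neither prescribes nor treats. *Outcome assessment* says: "Outcomes will be measured by physical therapists with at least 5 years of clinical experience". *Statistical analysis* says: "The statistician, who is blinded to the allocation, will perform the analysis".

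**The concern.** A code-break is normally justified because someone must know the treatment in order to look after the patient. Here the need for a medical work-up is enough, and many work-ups can be done without knowing the gel. Some of the symptoms that could prompt one are recognised effects of the active drug, so the trigger may itself be related to treatment.

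If so, the allocation becomes known to the investigator more often in one arm. What is at stake is the safety comparison. Once the code is open, whether the event is put down to the gel, and how it and any later event in that woman are recorded, can be influenced by knowing what she received. The *Discussion* presents the double-blind design as a main strength, so avoidable breaks are worth preventing.

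There is also an inconsistency. In the blinding section, code access goes together with exclusion. In the adverse-event section, even significant or severe events lead to an individual decision on continuation. Read literally, a minor symptom that needs a work-up could end in exclusion while a severe event is left to judgement.

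**Working it through.** **The two sections side by side**

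| Question | Blinding section | Adverse events section |
|---|---|---|
| What triggers action? | An adverse symptom needing further medical investigation; no grade given | A significant or severe event |
| Is the code involved? | Yes, the investigator may access it | Not mentioned |
| What follows for the woman? | Exclusion | Case-by-case decision to continue or withdraw |
| Who acts? | The investigator | The review board (CRB) or the chief investigator |

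The first row shows that the trigger is not tied to the article's own grading. The second shows that the article manages its gravest events without calling for the code. The third row is a direct conflict.

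**The plan's own figure, for the denominator**

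Inputs from *Sample size and power analysis*: effect size 0.6, one-sided 5% alpha, 80% power, about 10% dropout.

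- Normal approximation: 2 × (1.645 + 0.842)² / 0.6² = 34.4, so 35 per group.
- The t-test has power 79.96% at 35 and 80.9% at 36, so 36 is right.
- 36 / 0.90 = 40 per group.

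The stated 36 and 40 reproduce and are not in dispute. They supply only the 40 used below.

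**Expected code-breaks**

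The article gives no rate of such symptoms in either arm, so the rates here are assumptions. Expected breaks = 40 × rate; active share = active / (active + placebo).

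| Oestrogen rate | Placebo rate | Oestrogen breaks | Placebo breaks | Active share |
|---|---|---|---|---|
| 5% | 5% | 40 × 0.05 = 2 | 2 | 2/4 = 50% |
| 10% | 5% | 40 × 0.10 = 4 | 2 | 4/6 = 67% |
| 20% | 5% | 40 × 0.20 = 8 | 2 | 8/10 = 80% |

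The placebo rate is not set to zero. The listed minor events include complaints that can arise without oestrogen at ages 65 to 90, and the placebo gel contains ethanol. At equal rates there is no imbalance; it comes wholly from the excess on oestrogen, which the article does not quantify. The table also assumes that the code is opened every time, whereas access is only permitted.

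**Who could be influenced**

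The rule gives the code to the investigator. It does not give it to the physical therapists who measure outcomes or to the statistician. Each break reveals one woman's allocation, and stratification with mixed block sizes limits what it reveals about others. That leaves attribution and recording of adverse events in the unblinded woman, to the extent that the investigator who opened the code takes part in them.

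**The case against.** The strongest reply is that the rule does little harm. Access is optional and the situation is called unlikely. Whether a symptom needs investigation is judged before the code is opened. The outcome assessors and the statistician are not recipients. Release routes and logs belong in the full protocol, and the article says that a standardised adverse-event protocol and a manual are held at the hospital.

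Much of this stands. The absence of a release procedure or log from the article is not a fault. The trigger and the recipient, however, are stated, and they are stated broadly.

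Four stronger readings are tempting, and the documents do not support them:

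- **Code-breaks will cluster on oestrogen.** This is plausible, but no rates are given, and assuming almost none on placebo is too favourable to the point.
- **The person who judges events and continuation is unblinded.** One section says the investigator; the other says the CRB or the chief investigator. Nobody is named as grading events. Overlap is likely, since the chief investigator prescribes the gel, but it is not stated. Under the blinding section the woman is excluded anyway, so no later decision on her continuation remains.
- **The chair stand test is compromised.** Nothing shows that the physical therapists learn the allocation. That they might hear of it informally is conjecture.
- **Unblinded women drop out of the analysis.** The full analysis set is "defined as all the randomised participants who have started their trial treatments", which would keep them. What exclusion means for their follow-up is unclear, and is a separate matter from who is unblinded.

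**Conclusion.** The point holds in a limited form. The article permits unblinding without a need to know, on a trigger that recognised oestrogen effects could meet, and couples it with an exclusion that conflicts with its own adverse-event section. Avoidable breaks are possible and plausibly more frequent on oestrogen.

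The size is uncertain: 2 against 2 to 8 breaks of 40 per arm, resting on assumed rates of 5% on placebo and 5% to 20% on oestrogen, with every permitted access used. At the lower end there is no imbalance. The direct consequence is for attribution and recording of adverse events in the women concerned. An effect on the primary outcome is not shown. The change is worth making because it is specific and cheap, not because the trial's main comparison is in danger.

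**What to change.** In *Randomisation, allocation, and blinding procedure*, reword the trigger so that the code is opened only when knowledge of the allocation is needed for the woman's care. Have the existing unblinded pharmacist release it to the clinician who needs it. It should not be passed on to the outcome physiotherapists, exercise instructors, statistician or other study staff. That clinician may be an investigator, so a blanket rule that investigators stay blinded could be unworkable; where this happens, record it. Log each break with date and reason, and report the number by arm.

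Reconcile this section with *Adverse events* on whether a code-break, or a symptom work-up alone, leads to exclusion. Which rule should apply is for the investigators and is not proposed here. Investigation and care of symptoms stay unchanged.

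The cost is an amendment, with advance approval by the review board if it counts as substantial, a short log, and one call to the pharmacist when a code is needed. The number of breaks this would prevent cannot be stated from the documents.

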### Sample size and power analysis

The sample size calculations were based on previously published data on increased lower extremity strength with MRE and ERT [47]. The rate of increase in the muscle strength during ERT is 5%–17% [34]. Positive correlations (*r* = 0.75) have been reported regarding the relevance of CS-30 scores on knee extension strength [47]. The average CS-30 score in patients with KOA is 9.2 repetitions [48]. Assuming that ERT can be expected to increase the CS-30 score by 13%, this sample size allows the detection of 1.2 times the primary outcome improvement (increased CS-30 score), in addition to an increase of 2.68 repetitions (1.90–3.47 repetitions, *p* < 0.001; I2 = 0.50%) due to the MREP alone [49]. The required sample size is 36 persons per group, calculated with an 80% one-sided test setting power, 5% alpha, and a 0.6 effect size (Cohen's d). The target size is set to 40 per group to account for a dropout rate of approximately 10%. Reports have shown that ERT has a low-to-moderate effect on lower extremity strength [34, 49, 50] and that ERT has improved knee pain and joint function in patients with KOA [29, 31]; therefore, we assume that ERT will have a slightly larger-than-moderate effect.

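### Opening a woman's treatment code excludes her from the trial, which either breaks the intention-to-treat set or needlessly loses chair-stand values still due

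*Protocol article*

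**What the plan says.** The rule is in the section on randomisation, allocation and blinding. After an adverse symptom that needs further investigation, described there as unlikely, "the gel allocation details can be accessed by the investigator, and the patient will be excluded from the trial".

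Other sections bear on what this means:

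- **Statistical analysis** sets the target population as the full analysis set, "defined as all the randomised participants who have started their trial treatments". It names intention-to-treat and per-protocol analyses and makes no exception for a woman whose code was opened. The Abstract also commits to intention-to-treat. Missing outcomes are handled by complete-case analysis below 5% and by multiple imputation above 5%.
- **Medical assessment** uses the same phrase for women who fail screening: "the participant will be excluded from the trial and referred for further examination".
- **Adverse events** uses different terms. After a significant or severe event, "the CRB or CI will determine whether the participants can continue with or withdraw from the trial". Care continues regardless: "These participants will be referred and treated for each event depending on the symptoms and severity, even if they are withdrawn from the trial".
- **Study design** describes a "double-blinded RCT with a 12-week intervention period, and the outcomes will be measured at baseline, 3 months, and 12 months", and **Outcome assessment** makes the CS-30 changes at 3 and 12 months the primary outcome.

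**The concern.** The rule ties two separate decisions together: whether a woman goes on using the gel, and whether she goes on being measured. Learning her allocation may bear on the first. It has no necessary bearing on the second.

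The trigger occurs after randomisation and may depend on treatment. The protocol's adverse-event lists include irregular and heavy vaginal bleeding and tender breasts. These are plausible oestrogen effects, and some of them would call for investigation. If code breaks are commoner on oestrogen, and the women concerned would have scored differently from the rest, the comparison of observed outcomes is no longer the randomised comparison. The documents do not show that this dependence exists.

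The rule also sits awkwardly with the Adverse events section. That section leaves continuing or withdrawing after a significant or severe event to a decision by the review board or chief investigator. The code-break rule removes that choice, though only for a woman with such an event whose code is also opened.

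**Working it through.** **What the rule does on each reading**

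1. *Removed from analysis.* The screening section uses the phrase for women who never enter the trial. Applied in that sense to a randomised woman who has started gel, it takes her out of a set defined to include her. That contradicts the full analysis set and the intention-to-treat commitment.
2. *Withdrawn from the study.* She remains in the full analysis set, so nothing is contradicted. Her remaining CS-30 values are not collected: both visits if the code is opened before month 3, only the 12-month visit if it is opened later. The article provides for her medical care after withdrawal but not for outcome follow-up.

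The gel lasts 12 weeks, so at 12 months every woman is due to have been off gel for about 9 months. Having stopped early is no reason to skip that visit.

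**The plan's own sample size**

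Inputs (Sample size and power analysis): d = 0.6, one-sided 5%, 80% power, about 10% dropout. By the noncentral t, 35 per group gives 79.96% and 36 gives 80.9%, so 36 is the smallest group size that reaches 80%. 36/0.9 = 40. The stated 36 and 40 reproduce.

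**Scale for the illustration**

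- 13% of 9.2 repetitions = 1.196, about 1.2. I read the protocol's 1.2 as repetitions.
- Implied SD = 1.2/0.6 = 2.0.
- Standard error of the arm difference: 2 × √(2/40) = 0.447 at 40 v 40; 2 × √(2/36) = 0.471 at 36 v 36.

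**Bias**

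The documents give neither a code-break rate nor a CS-30 gap, so both are assumed. If k women per arm of 40 are lost and would have scored a fixed gap below the rest:

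bias = (k oestrogen − k placebo)/40 × gap

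| Lost, oestrogen v placebo | Gap (repetitions) | Bias (repetitions) | Share of 1.2 |
|---|---|---|---|
| 1 v 0 | 1 | 0.025 | 2.1% |
| 3 v 0 | 1 | 0.075 | 6.3% |
| 3 v 0 | 2 | 0.15 | 12.5% |
| 2 v 1 | 1 to 2 | 0.025 to 0.05 | 2.1% to 4.2% |
| 2 v 2 | equal | 0 | 0% |

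Against the standard error at 36 v 36, the extremes are 0.025/0.471 = 0.05 and 0.15/0.471 = 0.32.

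**Does the missing-data rule repair it?**

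Three losses alone are 3/80 = 3.75%, so complete-case analysis applies and the women are dropped. At the planned dropout, 8/80 = 10%, imputation applies. In a simulation (20,000 runs, 40 v 40, four missing per arm, three of the oestrogen losses being code breaks with gap 2), the bias was 0.149 with complete cases and 0.149 with multiple imputation conditioning on arm only, against 0.150 expected. With one code break and gap 1 it was 0.026 for both, against 0.025 expected (simulation error 0.003). Informative covariates could reduce this. The article does not state the imputation model.

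**Power** (noncentral t, one-sided 5%, d = 0.6)

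| Analysed, oestrogen v placebo | Power |
|---|---|
| 40 v 40 | 84.5% |
| 37 v 40 | 83.2% |
| 36 v 36 | 80.9% |
| 33 v 36 | 79.4% |

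The last row is three exclusions on top of the planned dropout. Power is not the issue.

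**The case against.** The strongest reply is that this is a blinding procedure and not an analysis rule. The analysis population is fixed in the Statistical analysis section, so the natural reading is withdrawal, and the screening section says little about what the phrase means for a randomised woman. Withdrawal is then ordinary dropout, which the plan anticipates with 40 per group and imputation. That withdrawal is the likelier reading stands, and on it there is no contradiction with the analysis set. But the loss is then created by rule, not by the woman's choice or condition. No analysis plan can recover values that were never measured.

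Second, the event behind the code break may itself prevent the test. After suspected thrombosis or anaphylaxis, a chair-stand test may be inappropriate. This is true for some women. It supports a case-by-case decision, which the Adverse events section already provides, and not a blanket exclusion triggered by opening the code.

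Third, the size rests on assumptions. The event is called unlikely, access to the allocation is discretionary, tender breasts and irregular bleeding are listed as minor events, and nothing in the documents links such events to lower CS-30 scores. The top figure needs three losses to none, each a full SD below the rest. The simulated imputation used arm only, whereas baseline CS-30 will be available. All of this stands. It limits the likely harm to something small, but it gives no reason to keep the rule.

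**Conclusion.** The concern holds. Followed as written, the rule either removes a randomised and treated woman from the analysis or stops collection of primary-outcome values that could still be obtained. Nothing in the article offsets the loss, and imputation may repair it only in part.

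The size and direction of any bias are unknown and probably small. The range of 0.025 to 0.15 repetitions assumes an SD of 2.0, one to three code breaks all in the oestrogen arm, and a gap of 1 to 2 repetitions. It falls to zero when numbers and gaps are equal across arms. Safety care is not in dispute. This should be fixed because the remedy is simple and uses visits already planned, not because large damage is likely. Confidence is medium, mainly because the intended meaning of the phrase is uncertain.

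**What to change.** Replace the exclusion clause in the randomisation and blinding section with wording such as:

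> Study gel is stopped if clinically needed. The participant remains in the full analysis set in her randomised group and, if she consents, CS-30, the other outcomes and safety are still assessed at 3 and 12 months by assessors unaware of her allocation.

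Leave any decision on withdrawal to the Adverse events section, so that the two sections agree, and exclude her only from the per-protocol set.

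The cost is a one-sentence amendment. The sample size does not change and no visits are added. The downside is that a few outcomes will come from women whose allocation is known to the investigator, which is why the outcome assessors should stay blinded.
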